### Methods in analysis to handle protocol non-adherence and any statistical methods to handle missing data {20c}

The primary analysis will follow the intention-to-treat (ITT) principle, including all randomized participants regardless of protocol deviations. A secondary per-protocol (PP) analysis will exclude patients with major deviations (e.g., incorrect biopsy allocation, inadequate imaging quality). Missing outcome data will be addressed primarily through multiple imputation techniques assuming missing at random. Sensitivity analyses include complete-case analysis and worst-case imputation for key endpoints.

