### Criteria for discontinuing or modifying allocated interventions {11b}

Because PRIMA is a diagnostic accuracy trial without therapeutic intervention, no modification or dose adjustment of assigned study procedures is possible. However, allocated biopsy procedures may be discontinued or deferred for an individual participant under the following circumstances:Participant decision or withdrawal of consent at any point prior to or during the biopsy procedure, without a requirement to provide justification and without any impact on subsequent clinical care.Medical judgment of the responsible study physician, if performing the biopsy would expose the participant to unacceptable clinical risk (e.g., acute infection, severe bleeding disorder, anticoagulation that cannot be safely paused, or significant deterioration in health status).Safety considerations arising during the procedure, including uncontrolled pain, vasovagal reaction, or procedure-related complications.Protocol deviations mandated by emergency clinical indications, if continuation is deemed inappropriate for patient safety.

Participants who discontinue or do not complete their allocated intervention will be encouraged to remain in the study for follow-up assessments where possible, and data already collected may be included in analyses according to the predefined statistical plan (intention-to-treat principle).

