### Outcomes {12}

#### Co-primary outcomes

Detection of clinically significant prostate cancer (csPCa; ISUP ≥ 2)

Defined as the presence of csPCa on histopathology at initial biopsy (measure: histopathological assessment; metric: binary yes/no). Results will be expressed as the proportion of participants with csPCa in each study arm (method of aggregation: proportion), assessed at index biopsy (timepoint).Detection of clinically insignificant prostate cancer (ISUP 1)

Defined as the presence of ISUP grade group 1 cancer on histopathology at initial biopsy (measure: histopathological assessment; metric: binary yes/no). Results will be expressed as the proportion of participants with ISUP 1 cancer in each study arm, assessed at index biopsy.

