## Assignment of interventions: blinding

### Who will be blinded {17a}

Clinical teams cannot be blinded due to procedural differences between study arms. Radiological assessment (including PI-RADS scoring) is performed prior to randomization and is therefore inherently blinded to treatment allocation. Biostatistical analyses will be conducted on pseudonymized datasets, with treatment allocation unmasked only after database lock, following finalization of the statistical analysis plan.

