## Statistical methods

### Statistical methods for primary and secondary outcomes {20a}

The primary analysis will compare the detection proportion of clinically significant prostate cancer (csPCa; ISUP ≥ 2) between Arm A (TB only) and Arm B (TB + SB) using a non-inferiority framework. Non-inferiority for csPCa detection will be assessed based on the absolute difference in detection proportions (π_TB − π_TB + SB), evaluated using the likelihood score test by Gart and Nam for binomial parameters at a one-sided α level of 0.05. The non-inferiority margin is δ = 13%. Superiority testing for the secondary co-primary endpoint (detection of clinically insignificant PCa, ISUP 1) will be evaluated based on the ratio of detection proportions (π_TB/π_TB + SB) using a one-sided α level of 0.05. All hypothesis tests apply a fixed global significance level of *α* = 0.05.

Secondary outcomes—including biopsy-related complications, biopsy avoidance, diagnostic performance measures, and biopsy approach comparisons—are defined in the Outcomes section according to domain, measurement, metric, method of aggregation, and timepoint. Biopsy-related complications will be summarized as proportions by study arm at 30 days post-procedure. Biopsy avoidance will be reported as the proportion of participants not undergoing biopsy following mpMRI triage at screening. Diagnostic performance outcomes (e.g., DRE, bpMRI vs mpMRI) will be evaluated using standard accuracy measures (e.g., sensitivity, specificity) where applicable.

All detection outcomes are defined as proportions (number of participants with the outcome divided by the number of participants undergoing biopsy in the respective arm). Secondary outcomes will be analyzed descriptively and, where appropriate, using inferential statistical methods.

Patient-reported outcomes (EPIC-26, EORTC-QLQ-C30, VAS) will be analyzed using mixed models for repeated measures (MMRM), including treatment arm, timepoint, and baseline values as covariates.

A detailed statistical analysis plan (SAP) will be finalized and archived prior to database lock and prior to any unblinded analyses.

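### Cheap improvement: the csPCa non-inferiority conclusion rests on ITT alone, so systematic biopsy given in Arm A or omitted in Arm B makes non-inferiority easier to declare

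*Protocol article*

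**What the plan says.** Section {20c} sets the analysis populations. On the primary analysis: "The primary analysis will follow the intention-to-treat (ITT) principle, including all randomized participants regardless of protocol deviations". On the other population: "A secondary per-protocol (PP) analysis will exclude patients with major deviations (e.g., incorrect biopsy allocation, inadequate imaging quality"). Neither this section, nor {20a}, nor the sample size section {14} says that the per-protocol (PP) result must agree before non-inferiority is concluded. The sensitivity analyses named in {20c}, complete-case and worst-case imputation, deal with missing outcomes.

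The csPCa co-primary outcome in {12} reads: "Defined as the presence of csPCa on histopathology at initial biopsy". It does not say that only cores belonging to the allocated strategy count. Section {20a} states the margin ("The non-inferiority margin is δ = 13" percent) and a one-sided 5% level.

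On the setting, {17a} says: "Clinical teams cannot be blinded due to procedural differences between study arms". Among the grounds in {11b} for discontinuing or deferring an allocated biopsy is: "Safety considerations arising during the procedure, including uncontrolled pain, vasovagal reaction, or procedure-related complications". For men who do not complete the allocated procedure, {11b} adds: "data already collected may be included in analyses according to the predefined statistical plan (intention-to-treat principle").

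**The concern.** As allocated, the arms share the targeted biopsy (TB) and differ only in the systematic cores. Two deviations therefore bear directly on the contrast. If an Arm A man also receives systematic cores and they alone show csPCa, ITT credits the finding to TB alone. If an Arm B man has TB without SB, ITT counts his TB-only yield as the yield of the combined strategy. Both shrink the difference as long as SB finds additional csPCa, which {14} assumes.

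In a superiority trial such dilution works against the claim. In a non-inferiority trial it works for it. A plan that decides on ITT alone has no safeguard if adherence turns out worse than hoped, and the stated 5% error rate holds only without such switching. The sensitivity analyses in {20c} do not help, because these men have an observed histology result. What is at stake is a conclusion that SB can be omitted, which the Discussion intends for guideline and reimbursement decisions.

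**Working it through.** **Inputs from the protocol.** Section {14}: 477 per arm, Arm B csPCa rate 50%, planned difference −5 points, 80% power, one-sided α 0.05. Section {20a}: margin 13 points and a likelihood score test.

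**The plan's own figure.** With the score-test variance, the rates restricted to a difference of −0.13 are 0.4105 and 0.5405.
- Null SD: s0 = √(0.4105×0.5895 + 0.5405×0.4595) = 0.7003.
- SD under 45% versus 50%: s1 = √(0.2475 + 0.25) = 0.7053.
- n = [(1.645×0.7003 + 0.842×0.7053)/0.08]² ≈ 476.02, rounded up to 477.
- Power at 477 is 80.1%.

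The stated sample size reproduces. The unpooled variance gives 481 per arm, or 79.7% power at 477.

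**Effect of switching.** Let a be the share of Arm A given SB, b the share of Arm B without SB, and D the true loss from omitting SB. Assume that switching is unrelated to risk.
- Arm A observed rate = 0.50 − D + aD.
- Arm B observed rate = 0.50 − bD.
- Expected ITT difference = −D(1 − a − b).
- P(declare non-inferiority) = Φ[(difference + 0.13)/SE − 1.645], with SE from the observed rates and n = 477.

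Example with D = 0.13 and a = b = 0.10: the rates are 0.383 and 0.487, the difference is −0.104 and the SE is 0.0319. So 0.026/0.0319 − 1.645 ≈ −0.83, and Φ(−0.83) ≈ 0.203.

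**True loss exactly at the margin (D = 13 points). The switching rates are assumptions.**

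| Arm A with SB / Arm B without SB | Expected ITT difference | P(declare NI), unpooled | P(declare NI), score |
|---|---|---|---|
| 0 / 0 | −13.00 | 5.0% | 5.0% |
| 1% / 1% | −12.74 | 5.9% | 5.9% |
| 2% / 2% | −12.48 | 6.9% | 6.9% |
| 5% / 5% | −11.70 | 10.8% | 10.9% |
| 10% / 10% | −10.40 | 20.3% | 20.5% |

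With 5% switching in one arm only, whichever arm it is, the figure is 7.5%.

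**At the planned −5 points**, the chance of declaring non-inferiority (score formula) rises from 80.1% to 84.1% at 5%/5% and 87.6% at 10%/10%.

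**Behaviour of PP.** In a simulation (200,000 runs, Wald test, random switching, D = 13 points), PP declared non-inferiority in 4.9% of runs at 5%/5% and 4.8% at 10%/10%. ITT did so in 10.4% and 19.8%.

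**Price in power.** Removing 5% per arm leaves about 453 men, and removing 10% leaves about 429. The score formula at −5 points then gives PP power of about 78% and 76%. The simulation gave 78.6% and 75.6%.

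**The case against.** The strongest reply is that adherence may be nearly complete. Section {11c} expects it to be high and has it reviewed monthly, and {11a} adds monitoring of implementation. At 1% or 2% switching per arm the error is 5.9% or 6.9%, a modest inflation. This stands as a limit on the likely size. It does not change the direction, and the decision rule offers no protection if the expectation fails.

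Second, a PP analysis is already planned and its list of deviations is only illustrative. An Arm A man given SB may well fall under incorrect biopsy allocation, and the statistical analysis plan can complete the list. This also stands: a short list of examples is no fault. What remains is that PP has no stated part in the conclusion.

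Third, PP drops men after randomization and can be biased if deviations relate to risk. Requiring both analyses is also a convention rather than the only valid design. That is a reason to use PP alongside ITT and not in its place.

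Two stronger readings are tempting, and the document does not support them.
- A reader might infer that an Arm B biopsy stopped midway is scored as showing no csPCa. No section says so. {11b} only allows data already collected to be used, and {20c} sends missing outcomes to multiple imputation. A man whose cores already show csPCa is positive in any case, and partly completed SB keeps some yield. Stopping can also occur in Arm A, where an incomplete TB works against non-inferiority. That stopping is more frequent in Arm B is conjecture.
- A reader might infer that external combined biopsies are a free route into Arm A. Section {11d} does not prohibit them, but it strongly discourages them, requires documentation and permits withdrawal. Nothing says such a biopsy counts as the index biopsy.

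**Conclusion.** The point holds as a cheap improvement, not as an error in the plan. ITT alone decides csPCa non-inferiority, and SB given in Arm A or omitted in Arm B pulls that analysis toward the claim. The direction rests on two premises: SB adds csPCa, as {14} assumes, and csPCa counts whichever cores show it. The second is a reading of {12}, which sets no restriction.

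The size cannot be known from the document. Across assumed rates of 1% to 10% per arm, the error at the margin runs from about 6% to about 20%, against a nominal 5%. The Arm B share of this is an upper bound, because it treats every deviating man as having had no SB at all, and incomplete TB in Arm A would offset part of it.

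A separate matter should be reconciled. Section {20a} defines the denominator as "number of participants with the outcome divided by the number of participants undergoing biopsy in the respective arm", while {20c} includes all randomized men. It does not affect this point, since the men concerned here were biopsied and are counted under both definitions.

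**What to change.** State in {20a} and {20c} that csPCa non-inferiority is concluded only if the lower confidence bound for the difference lies above −13 points in both the ITT and the PP analysis. For this purpose, PP excludes Arm A men who had any systematic cores, and Arm B men whose systematic cores were not completed, at the index biopsy.

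Add one ITT sensitivity analysis in which Arm A men are scored on their targeted cores only. This removes the Arm A route without excluding anyone, but leaves the Arm B route untouched. Keep ITT primary for the ISUP 1 superiority test.

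The cost is wording in the protocol and the analysis plan, and case report forms that hold targeted and systematic results separately if they do not already. No participant had been enrolled at submission, so the change can precede recruitment data. The statistical price is power. PP power at the planned −5 points falls from about 80% to roughly 78% with 5% and 76% with 10% deviating per arm, and the chance that both analyses succeed cannot exceed that. The sponsor should either accept this or allow for it in the sample size.

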### Plans to give access to the full protocol, participant level-data and statistical code {31c}

The full study protocol and statistical analysis plan (SAP) will be publicly accessible upon publication of the main results. Participant-level pseudonymized datasets and statistical code will be made available upon reasonable request to the corresponding author after completion of primary analyses and institutional review, in accordance with GDPR and data governance regulations.

## Oversight and monitoring

### Composition of the coordinating center and trial steering committee {5d}

The coordinating center for the PRIMA trial is located at the University Hospital Düsseldorf and is responsible for day-to-day operational management, site communication, regulatory coordination, investigator training, and monitoring oversight. The German Cancer Research Center (DKFZ), Heidelberg, oversees biostatistical infrastructure, including randomization processes, data management systems, and final statistical analysis.

The Trial Steering Committee (TSC) provides scientific oversight, monitors trial progress, evaluates protocol adherence, resolves methodological and logistical issues, and approves protocol amendments. The TSC meets monthly, or more frequently if required. The committee is composed of the Principal Investigators and all co-applicants (see also 5a). The committee receives operational support from the coordinating center trial office, which manages cross-site communication, documentation control, quality assurance processes, and adherence to trial timelines.

### Composition of the data monitoring committee, its role and reporting structure {21a}

A Data Monitoring Committee is not required given the low-risk, diagnostic nature of the trial. Independent data and safety monitoring will be performed by the German Cancer Research Center according to Good Clinical Practice standards.

### Adverse event reporting and harms {22}

Adverse events (AEs) and serious adverse events (SAEs) related to biopsy procedures will be collected systematically from the time of intervention up to 30 days post-biopsy and documented in the electronic case report forms. In addition, specific complications will be actively assessed at 30 days using a structured patient survey, including sepsis, hospitalization, bleeding, urinary retention, persistent pain, hemospermia, and urinary tract infection.

SAEs will be reported to the sponsor and relevant ethics committees in accordance with national regulatory requirements. All events will be reviewed by the coordinating investigators.

In publications, all collected adverse events will be reported descriptively by study arm, including frequencies and severity grading. Serious adverse events and clinically relevant complications will be reported in detail to ensure transparent and comprehensive safety reporting.

The frequency and nature of biopsy-related complications are predefined secondary outcomes.

### Frequency and plans for auditing trial conduct {23}

Independent monitoring will be performed according to a risk-adapted monitoring plan and performed by qualified personnel independent of the investigators and sponsor. On-site monitoring visits will be conducted at least annually, with additional remote monitoring for consent documentation, endpoint verification, and source data consistency. Monitoring activities include verification of adherence to the protocol, data accuracy, informed consent procedures, and reporting of adverse events. Audit results and corrective actions will be documented and communicated to participating centers and the TSC.

### Plans for communicating important protocol amendments to relevant parties (e.g., trial participants, ethical committees) {25}

Any important protocol modifications (e.g., changes to eligibility criteria, sample size, outcomes, or analytic strategy) will be communicated to all relevant stakeholders, including participating investigators, ethics committees, regulatory authorities, trial registries, and study participants, where applicable. Updated protocol versions will be resubmitted to registries (ClinicalTrials.gov) and annotated within future publications. Changes will also be documented within the electronic trial master file and circulated through official newsletters and site investigator meetings.

### Dissemination plans {31a}, {31b}

Results will be disseminated through peer-reviewed open-access publications, scientific conferences, and patient stakeholder organizations irrespective of study outcome. Authorship will follow ICMJE guidelines. The full protocol, statistical code, and de-identified dataset will be made available upon reasonable request after publication.

## Discussion

The PRIMA study is designed to resolve a central question in modern prostate diagnostics: is systematic biopsy still required for biopsy-naïve men in the era of high-quality mpMRI and fusion-guided TB? Current evidence remains mixed. Trials such as PRECISION [8], MRI-FIRST [9], and 4-M [10] confirmed that mpMRI-guided TB achieves high csPCa detection, but residual incremental detection from SB remains. Screening trials like STHLM3-MRI [11] and Göteborg-2 [12] further emphasized that omitting SB reduces overdetection but carries a marginal risk of missing csPCa. Thus, guidelines differ internationally, and a definitive, high-quality randomized trial within a controlled QA environment is urgently needed. Compared to prior studies, PRIMA features several distinguishing elements. First, strict preselection limits biopsy to men with PI-RADS 4/5 or PI-RADS 3 with PSAD > 0.15, consistent with German guideline recommendations [15, 24]. This enriched population minimizes unnecessary biopsies while maintaining csPCa yield. Second, mpMRI is mandatory rather than optional or replaced by bpMRI, ensuring maximal lesion characterization, especially in younger cohorts where imaging interpretation is more challenging [18, 19]. Third, uniform QA through PI-QUAL and operator certification standardizes both imaging and biopsy performance across all sites. Finally, inclusion of PROs allows holistic assessment of diagnostic burden, patient satisfaction, and complication profiles. The study also integrates advanced research objectives such as AI and radiomics model validation. By linking imaging features, histopathology, and PRO data, PRIMA aims to establish predictive algorithms for csPCa and quality-of-life outcomes, providing a platform for future personalized diagnostics. Expected benefits include reduced biopsy numbers, lower infection rates, and fewer ISUP 1 detections—leading to substantial health-economic savings [2, 3, 7]. Conversely, if SB omission compromises csPCa detection, results will clarify which subgroups (e.g., age, prostate volume, PI-RADS 3) still benefit from combined sampling. The standardized design and large sample will support guideline updates, reimbursement decisions, and possible nationwide implementation of MRI-only pathways if non-inferiority is demonstrated. Lastly, the PRIMA trial will further assess under which conditions and to what extent MRI in-bore biopsy constitutes a valid and safe approach within a targeted biopsy-only paradigm [25–28]. Limitations include potential selection bias toward academic centers with strong MRI expertise and limited generalizability to less-specialized institutions. Nevertheless, PRIMA’s rigorous QA, centralized monitoring, and defined endpoints ensure validity and reproducibility. Its findings will directly influence diagnostic policy, reduce overtreatment, and optimize early detection of clinically meaningful prostate cancer in Germany.

## Trial status

Protocol version v1.0, dated 15 January 2026. Recruitment is planned for 15 April 2026 and is expected to continue for 36 months. The anticipated completion of recruitment is 15 April 2029, with final follow-up ending approximately April 2030 and database lock projected for October 2030.

This article reports the initial approved protocol prior to recruitment. No participants have been enrolled at the time of manuscript submission.

## Data Availability

No datasets were generated or analysed during the current study.

## Abbreviations

AE: Adverse event
AI: Artificial intelligence
csPCa: Clinically significant prostate cancer
DCE: Dynamic contrast-enhanced MRI
DMC: Data Monitoring Committee
DRE: Digital rectal examination
DWI: Diffusion-weighted imaging
EPIC-26: Expanded Prostate Cancer Index Composite (26-item)
eCRF: Electronic case report form
GDPR: General Data Protection Regulation
GCP: Good Clinical Practice
ICMJE: International Committee of Medical Journal Editors
ISUP: International Society of Urological Pathology
ITT: Intention-to-treat
mpMRI: Multiparametric magnetic resonance imaging
MR: Magnetic resonance
PROM: Patient-reported outcome measure
PI-RADS: Prostate Imaging Reporting and Data System
PI-QUAL: Prostate Imaging Quality Score
PCa: Prostate cancer
PSA: Prostate-specific antigen
PSAD: PSA density
QA: Quality assurance
SAP: Statistical analysis plan
SB: Systematic biopsy
SAE: Serious adverse event
TB: Targeted biopsy
TR: Transrectal
TP: Transperineal
TSC: Trial Steering Committee
VAS: Visual analog scale
